## Methods – immunogenicity analyses

### PBMC sample processing

Peripheral blood mononuclear cells (PBMCs) were isolated from 8 mL whole blood drawn in heparinized cell preparation tubes (BD Vacutainer® CPT™) solution by standard venipuncture. Samples were processed within 2 hours of drawing by centrifugation according to the manufacturer's recommendations, washed with RPMI (Lonza / BioWhittaker) and cryopreserved in equal amounts of RPMI supplemented with 50% heat-inactivated fetal bovine serum (FBS) (Gibco by Life Technologies) and FBS with 20% dimethyl sulfoxide (DMSO) (Sigma Aldrich). Cells were immediately frozen at -80°C in CoolCell™ containers (Sigma Aldrich) and transferred to -150°C for storage. PBMCs were thawed in 37°C by placing cryovials directly from freezer into a waterbath at 37°C for 1-2 minutes until the cell suspension detached from the wall of the cryovial and transferred to 15mL tubes containing 100µL pre-warmed RPMI 1640 enriched with 10% FBS and 1% PenStepGlutamine (100X). Cryovials were washed out with 100µL medium followed by drop-wise resuspension of cell suspension in 1mL medium and addition of medium to total 10mL for washing. Supernatants were discarded after centrifugation and cell pellet resuspended in total 1mL medium before incubation for 4 hours (37°C, 5% CO2). Cell count and viability were assessed on stained cells using Muse™ Count & Viability kit and analyzed by the Muse™ Cell Analyzer (Merck, Germany).

### Fluorescence immuno-spot (Fluorospot) assay (IFN $\gamma$ /IL-2)

Peripheral blood mononuclear cells (PBMCs) were isolated from fresh blood (BD Vacutainer® CPT™) and 3x10^5 cryopreserved PBMCs per well (Human IFN $\gamma$ /IL-2 pre-coated FluoroSpot plates, 96-wells, Mabtech AB, Sweden), were set up in triplicates for 17 hour stimulation with co-stimulant (anti-CD28 0.1mg/ml, Mabtech AB, Sweden) and the following individual stimulants; ESAT-6, (2 µg/ml), Ag85, (2 µg/ml) (both 15mer overlapping peptide, Genscript, HK limited; >85% purity), culture filtrate protein-10 (CFP-10) (2µg/mL, 15mer overlapping peptide pools, >80% purity; Schäfer, Hadsund, Denmark), and the H56 fusion protein at 5µg/mL (Statens Serum institute, SSI). Samples were processed on a CTL Analyzer (LCC Cellular Technology Limited) according to the manufacturer's instructions and spot-forming units (SFU) were automatically counted applying the ImmunoSpot Software v.5.1 (2012) prior to manual quality control. A valid result required, >12 SFU for IFN $\gamma$  in positive control (anti-CD3 0.1mg/ml, Mabtech AB, Sweden) and  $\geq 2$  times the SFU in the negative control (RPMI 1640 L-Glutamine, Lonza/Bio Whittaker) (Essone et al., 2014). The immunological readouts were denoted as described in appendix (pp 7-8).

### Whole blood intracellular cytokine staining (WB-ICS) assay

Within 75 min of sampling, 1 ml of WB were incubated in the presence of co-stimulants (anti-CD28, 0.25µg/mL and anti-CD49d 0.25µg/mL) with separate peptide pools (ESAT-6, Ag85b and Rv2660c (2µg/mL, 15mer overlapping peptide, Genscript, HK limited; >85% purity) or Purified Protein Derivate (PPD, 10µg/mL, SSI) for 12h (Brefeldin A added after 7h) prior to fixation and cryopreservation (Kagina et al., 2015). ICS was done in one-step after a 10 min incubation (dark at room temperature) with 200µL Perm/Wash buffer (cat.no 554723, BD) followed by a 5 min centrifugation at 450-500 rcf and decantation: The 50 µL color mix per sample well included titrated volumes of CD3 AmCyan (clone SK7/Leu-4/cat.no 339186, BD, at 0.3125 µL), CD4 APC-H7 (SK3/Leu-3a/cat.no 641398, BD, at 0.625 µL), CD8 AlexaFluor488 (clone SK1/cat.no 344716, Biolegend, at 0.625 µL), IFN $\gamma$  BV421 (clone B27/cat.no 562988, BD Horizon, at 0.625 µL), TNF $\alpha$  APC (clone Mab11/cat.no 551384, BD Pharmingen, at 5.0 µL), IL2 PE (MQ1-17H12/cat.no 559334, BD Pharmingen, at 5.0 µL). The BD FACS Canto II flow cytometry with BD FACS Diva Software was applied, whereas data analysis was performed with the FlowJo Software version 10.4.1 (TreeStarInc, Ashland, OR, USA). The immunological readout Cytokine+ CD4 or CD8 T cells denoted producers of any of the measured cytokines. Other subpopulations are specified according to their cytokine production. All samples with an invalid positive control were excluded from analyses. Invalid positive control was defined as: Invalid if SEB induced tot IFN $\gamma$  response by CD4 is < 4 Medians of the tot IFN $\gamma$  response by CD4 T cells of the unstimulated controls of all participants in the study at the respective measurement time point

### Quantification of anti-H56 IgG in serum

To measure the anti-H56 IgG in human serum an indirect ELISA was developed at SSI. An in-house established human reference serum pool, assigned 200 ELISA units/ml (EU/ml) was used for assay optimization and calibration of unknown sera. NUNC MaxiSorb plates was coated with 50 µl of H56 (Batch DS-026-17, SSI), diluted to 0.2 µg/ml in Carbonate buffer pH 9.6 and incubated 2 hours at room temperature or overnight at 2-8°C. The Reference serum and test samples was in 2-fold serial dilution in parallel. For detection the plate was added HRP labelled HRP labelled Rabbit anti-human IgG (DAKO; P0214 / Cat. No. P021402-02), OPD substrate was added and the reaction was stopped with 1M H2SO4. OD (492 nm) was read using an ELISA reader. A reference line approach on log-log transformed data was used to calculate the concentration of anti-H56 IgG antibodies, with the reference serum pool as calibrator.

## Statistical methods – detailed description

The primary outcomes on safety were performed on the safety analysis set (SAS) (described in section statistical methods in article). The secondary outcomes of immunogenicity were assessed on the full analysis set (FAS). To acknowledge the possible impact of poor compliance to allocated treatment on immunogenicity, we calculated compliance for each group based on a priori definitions. For all arms, a participant was considered compliant if no corticosteroids/additional NSAIDs during the last seven days prior to sampling were taken. In addition, if allocated to etoricoxib,  $\geq 80\%$  of prescribed daily doses had to be taken during 1) the day 0-140 interval, and 2) the last 7 days prior to sampling. If allocated to H56:IC31-vaccine,  $\geq 1$  H56:IC31-vaccine were administered. The number (and percentage) of patients that were compliant with major treatment are presented but no per protocol analyses were performed.

### Primary endpoint: safety

The primary outcome is the occurrence of adverse events (AEs), serious adverse events (SAEs), and suspected unexpected serious adverse reactions (SUSARs) for the following time intervals:

- a. Day 0 to day 84 (or date of first vaccination if applicable).
- b. Day 85 (or date of first vaccination if applicable) to day 154 (or 14 days after last vaccination/last Arcoxia treatment, if applicable).
- c. Day 155 (or 15 days after last vaccination/last Arcoxia treatment, if applicable) to day 238.

If the second vaccination is missing, day 154 is defined as 70 days after the date of day 84.

AEs are defined as any unintended sign, symptom or disease in a participant receiving the treatment and which does not necessarily have to be causally related with the treatment. The AEs will be coded using the Medical Dictionary for Regulatory Activities (MedDRA 22).

SAEs are defined as a medical occurrence that results in death, is life-threatening, requires in-patient hospitalisation or prolongation of the existing hospitalisation, results in disabilities, is a congenital abnormality of birth defect, or requires medical intervention to prevent the outcomes mentioned above. If there is a doubt about an AE being serious or not, it is considered serious.

SUSARs are defined as SAEs that are unexpected as defined in the study protocol (V6\_121016), Section 8.1 and 8.2, pages 32-34 and possibly related to the study treatment.

We calculated the numbers and proportions of participants in the SAS that experienced an AE, SAE, and SUSAR by study arm and above defined three time intervals. We also calculated the number and proportions of participants with 1, 2, or  $\geq 3$  AEs, SAEs, and SUSARs; the number and proportion of participants with any treatment related AE and SAE; and, the number and proportion of participants with an AE/SAE leading to study drug discontinuation in each study arm and above defined three time intervals. No formal statistical testing of differences between the study arms was performed. Further, we described the total number of AEs, SAEs, SUSARs, treatment related AEs and SAEs, and AEs/SAEs leading to study drug discontinuation independent of number of participants. In addition, we described the absolute, number of participants with and proportion of participants with AE, SAE, SUSAR, severe AEs, and AEs leading to study drug discontinuation by system organ class (SOC) and preferred term (PT), without calculating any p-values.

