**Supplementary Table 9. Adverse events (AE) tables Day 0 to day 84. Safety Analysis Set\* (N=47)**

**Summary of AEs**

|                                                    | etoricoxib N=13 | H56:IC31 TB vaccine N=12 | Control N=12 | etoricoxib and H56:IC31 TB vaccine N=10 |
|----------------------------------------------------|-----------------|--------------------------|--------------|-----------------------------------------|
| Any AE                                             | 11 (84.6%)      | 11 (91.7%)               | 11 (91.7%)   | 9 (90.0%)                               |
| Number of AEs                                      | 58              | 45                       | 54           | 52                                      |
| Number of SAEs                                     | 2               | 0                        | 2            | 1                                       |
| Number of SUSARs                                   | 1               |                          |              |                                         |
| One AE                                             | 1 (7.7%)        | 4 (33.3%)                | 1 (8.3%)     | 1 (10.0%)                               |
| Two AEs                                            | 1 (7.7%)        | 2 (16.7%)                |              |                                         |
| Three or more AEs                                  | 9 (69.2%)       | 5 (41.7%)                | 10 (83.3%)   | 8 (80.0%)                               |
| Any SAE                                            | 2 (15.4%)       |                          | 1 (8.3%)     | 1 (10.0%)                               |
| Any SUSAR                                          | 1 (7.7%)        |                          |              |                                         |
| Any treatment related AE                           | 10 (76.9%)      | 0                        | 0            | 9 (90.0%)                               |
| Any treatment related SAE                          | 2 (15.4%)       |                          |              | 1 (10.0%)                               |
| Any AE leading to study drug discontinuation       | 2 (15.4%)       |                          | 1 (8.3%)     | 4 (40.0%)                               |
| Number of AE leading to study drug discontinuation | 2               |                          | 1            | 7                                       |

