|                                                      | Dyspepsia                                   | [1] 1 (7.7%)    | [3] 2 (16.7%)            | [2] 2 (16.7%) |                                         |
|                                                      | Gastritis                                   | [1] 1 (7.7%)    | [1] 1 (8.3%)             |               |                                         |
|                                                      | Haemorrhoids                                | [1] 1 (7.7%)    |                          |               |                                         |
|                                                      | Nausea                                      | [7] 6 (46.2%)   | [4] 4 (33.3%)            | [3] 3 (25.0%) | [6] 5 (50.0%)                           |
|                                                      | Vomiting                                    |                 | [1] 1 (8.3%)             |               | [1] 1 (10.0%)                           |
| General disorders and administration site conditions | Chest pain                                  | [1] 1 (7.7%)    | [3] 3 (25.0%)            |               |                                         |
|                                                      | Disease progression                         | [1] 1 (7.7%)    |                          |               |                                         |
|                                                      | Fatigue                                     | [9] 8 (61.5%)   | [4] 4 (33.3%)            | [6] 6 (50.0%) | [3] 3 (30.0%)                           |
|                                                      | Pyrexia                                     |                 |                          |               | [1] 1 (10.0%)                           |
|                                                      | Vaccination site pain                       |                 |                          |               | [2] 2 (20.0%)                           |
| Immune system disorders                              | Immune reconstitution inflammatory syndrome |                 |                          |               | [1] 1 (10.0%)                           |
| Infections and infestations                          | Lymph node abscess                          |                 |                          |               | [1] 1 (10.0%)                           |

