**Time-line (anti-TB chemotherapy, day 0-182)**

### Supplementary Figure 9

The safety profile of COX2i or H56:IC31 has not yet been determined in a population undergoing treatment for pulmonary TB. Therefore, we will enrol participants in two groups separated by a safety review. Group A includes volunteers for arm #1, arm #2 and arm #3 (2:2:1 randomization). First at the completion of Study Day 98 for all group A participants, the “clinical investigational group” (sponsor, PI, collaborators including representative from the H56:IC31 vaccine manufacturer) will meet and evaluate the cumulative safety data to determine if the observed safety profile meets the criteria to proceed to inclusion of volunteers for group B; arm #4 and remaining Arm #3 controls (2:1 randomization).

Arm #1 (n=10): etoricoxib treatment started at day 0 and given for 20 weeks (day 0-140) followed by 6 weeks (or according to clinical evaluation) of standard anti-TB chemotherapy alone (day 0-182) and follow-up control at day 210 and day 238.

Arm #2 (n=10): given anti-TB chemotherapy alone (day 0-182) (or according to clinical evaluation) and follow-up control at day 210 and day 238. TB vaccine H56:IC31 will be injected at day 84 and day 140.

Arm #3 (controls, n=10): given anti-TB chemotherapy alone (day 0-182) (or according to clinical evaluation) and follow-up control at day 210 and day 238.

Arm #4 (n=10): etoricoxib treatment started at day 0 and given for 20 weeks (day 0-140) followed by 6 weeks (or according to clinical evaluation) of standard anti-TB chemotherapy alone and follow-up control at day 210 and day 238. TB vaccine H56:IC31 will be injected at day 84 and day 140.

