## Visit 6- (day 84)

1. Record any adverse events, including serious adverse events and adverse events of special interest occurring since previous evaluation; record any concomitant medications taken associated with treatment of the adverse event.
2. Focused physical examination by medical practitioner if indicated based on history
3. Vital signs: Blood pressure, pulse, temperature. Weight.
4. Sputum samples
5. **Urine collection:** Confirm continued eligibility for vaccination including negative hcg (urine pregnancy test) for all females of child-bearing potential
6. **Blood collection/number of tubes:**
  - a. Serum chemistry/hematology: **1 EDTA tube (4 ml), 1 serum tube (5 ml).**
  - b. Blood hcg for all females of childbearing potential.
  - c. Biobank: **1 Natrium heparine tube\*(=WHOLE BLOOD), 4 CPT tubes, 1 Pax gene tube.**
7. Anti TB chemotherapy: standard combination therapy. Register any changes in medication in CRF
8. *Vaccine administration study arms #2 and #4:* Confirm subject identification number, check if patient is eligible to receive the study vaccine according to specific criterias. Check subject initials, date and time of dose preparation. Administer study vaccine to deltoid area by intramuscular injection. Record date and time of vaccination and which arm was vaccinated. Monitor subject for acute adverse events for at least 60 minutes after vaccination.
9. Examine site of vaccination 60 +/- 10 minutes post-immunization.
10. Drug dispensing and collecting: Collect and record any excessive study medication and empty medicine containers and if needed: hand out new study medication (Etoricoxib) for study arms #1 and #4. Register in drug accountability log.

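### The date of first vaccination closes safety interval a and opens interval b, so same-day dose 1 reactions can be filed as pre-vaccine events; the early-stop rule for etoricoxib can also make the intervals overlap

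*Protocol*

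**What the plan says.** The statistical methods description, under Primary endpoint: safety, defines the primary outcome as the occurrence of AEs, SAEs and SUSARs in three intervals, and makes all counts and proportions by arm and interval.

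- Interval a: "Day 0 to day 84 (or date of first vaccination if applicable".
- Interval b: "Day 85 (or date of first vaccination if applicable) to day 154 (or 14 days after last vaccination/last Arcoxia treatment, if applicable".
- Interval c: "Day 155 (or 15 days after last vaccination/last Arcoxia treatment, if applicable) to day 238".

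If dose 2 is missing, day 154 is set at 70 days after the date of day 84. Nothing there assigns an event that starts on the day of dose 1.

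Section 3 places dose 1 on the boundary itself: "TB vaccine H56:IC31 will be injected at day 84 and day 140". Appendix 6, Visit 6, looks for same-day reactions ("Examine site of vaccination 60 +/- 10 minutes post-immunization") and has their timing available ("Record date and time of vaccination and which arm was vaccinated"). Section 8.5 records date and time of onset for each AE, and Section 8.6 makes injection site pain a solicited event.

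**The concern.** Interval a is the time before any vaccine in arms 2 and 4, and interval b is where vaccine reactions should appear. When one date belongs to both, a reaction that starts an hour after the injection may go into either. The date is not an incidental one, because it is the day on which acute reactions are most actively sought.

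At stake is how the interval tables read for the combination arm, whose safety is a primary objective. A vaccine reaction in interval a is shown as if it came before the vaccine, over a denominator that includes people who were never injected. If an event could enter both intervals, the interval totals could not be added.

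**Working it through.** **1. Do the intervals share a day?** The document's own pattern is inclusive bounds: day 84 is followed by day 85, and 14 days by 15 days. With dose 1 on day v, interval a is days 0 to v and interval b starts on day v. The intersection is the single day v, whether v is 80, 84 or 90. For participants never vaccinated, days 0 to 84 and days 85 to 154 do not intersect.

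**2. Is interval c always clear of the others?** If the last dose is on day 140, b ends on day 140 + 14 = 154 and c starts on day 140 + 15 = 155, so there is no overlap. Now take, as an illustration, an arm 1 participant who stops etoricoxib on day 40 and stays in follow-up. Section 6.3.2 has rules for stopping etoricoxib that are separate from those for leaving the study in Section 6.3.1.

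- Interval a: days 0 to 84.
- Interval b: starts on day 85 and ends on day 40 + 14 = 54, before it begins.
- Interval c: starts on day 40 + 15 = 55.
- Overlap of a and c: days 55 to 84, which is 84 − 55 + 1 = 30 days.

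So the b/c rule is also not safe as written.

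**3. Reproduce the stated arm 4 totals.**

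- "Supplementary Table 9. Adverse events (AE) tables Day 0 to day 84": summing arm 4 events by system organ class in table order gives 2 + 10 + 6 + 1 + 1 + 1 + 4 + 1 + 5 + 5 + 1 + 1 + 1 + 3 + 9 + 1 = 52, as stated. The 6 under general disorders are fatigue 3, pyrexia 1 and "Vaccination site pain" 2.
- Supplementary Table 10 (day 85 to 154): 3 + 6 + 1 + 2 + 1 + 2 = 15, as stated. The 6 under general disorders include site pain 2, induration 1 and local reaction 1.

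**4. Site pain by table.**

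| | Day 0–84 | Day 85–154 |
|---|---|---|
| Arm 4 | 2 events in 2 of 10 (20.0%) | 2 events in 2 of 8 (25.0%) |
| Arm 2 | none | 1 event in 1 of 11 (9.1%) |

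Supplementary Table 8 shows that 8 of the 10 arm 4 participants received dose 1. The 20.0% therefore includes 2 people who could not have had a site reaction.

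**5. How can site pain fall in day 0 to 84?** Under the written definition, the only day in interval a on which it can start is the shared date. If the tables were instead cut at calendar day 84, a dose given early in the ±7-day visit window (from day 84 − 7 = 77) would put it there too.

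**6. Refile the 2 events.**

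- Arm 4, interval a: 52 − 2 = 50 AEs, with no site pain.
- Arm 4, interval b: 15 + 2 = 17 AEs if the 2 events are distinct from those already there, or 15 if both were listed twice.
- Sum of a and b: 50 + 17 = 67, or 50 + 15 = 65, against 52 + 15 = 67 as tabulated.
- Arm 4 participants with site pain: 2 to 4 of 8 injected (25% to 50%).

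**The case against.** The case for leaving this alone has several parts.

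- **Double counting.** A reader might infer from the matching 2 and 2 that the same events appear in both tables. The documents do not support that. Interval b also contains dose 2 at day 140, so dose 1 pain in a and dose 2 pain in b is a plain explanation. Arm 2 shows no sign of duplication, since its site events are all in interval b. Without onset dates or identifiers, duplication is possible but unproven.
- **Cause.** A reader might also infer that the shared date produced the misfiling. The table titles use calendar days, so a calendar cut with an early dose explains it equally well. This stands. On either account, vaccine reactions sit in the table meant to precede the vaccine.
- **Analysis plan.** The methods text cites a final statistical analysis plan that is not shown and may hold a tie-break. That would excuse a missing detail. Here the boundary is stated, and stated so that two intervals share a day.
- **Harm.** The 2 events are about 1% of all interval a AEs: 2 / (58 + 45 + 54 + 52) = 2/209. Site pain identifies itself as a vaccine reaction wherever it is listed, relatedness is assessed separately, and no between-arm test is made. This stands, and it limits the weight of the point.

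**Conclusion.** The definition is wrong as written and should be corrected, but the effect is minor. For vaccinees the date of dose 1 belongs to both a and b. For etoricoxib participants who stop early, c can begin before a ends. It would be a mistake to treat the dose 1 date as the only faulty boundary.

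The visible consequence is 2 site-pain events in arm 4 filed in day 0 to 84. They move interval a from 52 to 50 AEs and leave interval b between 15 and 17. The severe and serious tables contain no site event, and the safety analysis is descriptive.

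This assumes inclusive bounds, and that site pain coded to vaccination follows an H56:IC31 injection. The early-stop overlap follows from the wording alone. The document does not show how many participants stopped etoricoxib early and stayed in follow-up, so its effect on the tables is unknown.

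**What to change.** Rewrite the interval definitions under Primary endpoint: safety.

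- For vaccinated participants, end interval a just before the first injection. Assign every event with onset after it, including later on the same day, to interval b only. Same-day events without a recorded onset time also go to b.
- Count each event once, by onset.
- End b no earlier than day 154 (or 70 days after the date of day 84 when dose 2 is missing), and start c only after b ends. This keeps the intervals disjoint for participants who stop etoricoxib early.

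Then correct the day 0 to 84 and day 85 to 154 tables. Check the day 155 to 238 table too if any early stopper contributed events.

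The cost is a few sentences and a re-run of descriptive tables from onset and injection times that the protocol already requires. The default for untimed same-day events may move an occasional pre-injection event into b. That is the smaller error, because it does not hide a vaccine reaction in the pre-vaccine interval.

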**AE by System Organ Class (SOC) and Preferred term (PT) ([no. of events] no of patients (% of patients))**

| System Organ Class                                   | Preferred term                              | etoricoxib N=13 | H56:IC31 TB vaccine N=12 | Control N=12  | etoricoxib and H56:IC31 TB vaccine N=10 |
|------------------------------------------------------|---------------------------------------------|-----------------|--------------------------|---------------|-----------------------------------------|
| Blood and lymphatic system disorders                 | Anaemia                                     |                 |                          | [1] 1 (8.3%)  |                                         |
|                                                      | Leukopenia                                  |                 |                          |               | [1] 1 (10.0%)                           |
|                                                      | Lymphadenopathy                             |                 |                          | [1] 1 (8.3%)  |                                         |
|                                                      | Thrombocytopenia                            |                 |                          |               | [1] 1 (10.0%)                           |
| Gastrointestinal disorders                           | Abdominal discomfort                        | [1] 1 (7.7%)    |                          |               | [1] 1 (10.0%)                           |
|                                                      | Abdominal pain                              | [1] 1 (7.7%)    |                          |               | [2] 2 (20.0%)                           |
|                                                      | Abdominal pain upper                        | [1] 1 (7.7%)    | [1] 1 (8.3%)             | [2] 2 (16.7%) |                                         |
|                                                      | Diarrhoea                                   | [1] 1 (7.7%)    |                          |               |                                         |
|                                                      | Dry mouth                                   | [1] 1 (7.7%)    | [1] 1 (8.3%)             |               |                                         |

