### **7.2.7 Adverse Events (AEs)**

The adverse drug reaction (ADR) profiles for etoricoxib give reason to expect gastrointestinal AEs, especially nausea, as the most common (see section 8.2). Headache may also occur. In addition, study personnel must remain vigilant for the occurrence of any event related to the patients' TB diagnosis and anti-TB chemotherapy where gastrointestinal ADRs are the most common as well as to all other types of AEs.

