## 8.2 Expected Adverse Events (EAE)

**Etoricoxib**: Gastrointestinal EAE and headache are the most commonly occurring.  $\geq 1/100$  til  $< 1/10$ : abdominal pain, constipation, gastritis, reflux, gas, diarra, dyspeptic discomfort, nausea, vomiting, eosophagitis, palpitations, arrhythmia, hypertension, alveolar osteitis, increase in liver enzymes (ALAT/ASAT), bronchospasm, dizziness, headache, oedema, fatigue (text from Arcoxia, MSD, ATC-nr.: M01A H05 in Felleskatalogen). The EAEs will be recorded in the CRF.

**H56:IC31**: Vaccination with H56:IC31 has been associated most commonly ( $\geq 10\%$  of subjects with one or several of the AE) with mild to moderate injection site reactions of pain, warmth, and swelling, mild to moderate systemic adverse events of fatigue, bradycardia, myalgia, nausea, headache, arthralgia, and white blood cell count increased; and mild to severe hypertension (Table 5-8, page 72, Statens Serum Institut Investigator's Brochure).

There have been no suspected unexpected serious adverse reactions (SUSARs) reported to date in clinical trials of H56:IC31.

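### The safety tables count participants only per preferred term, so the proportion with any gastrointestinal event in the intervals of etoricoxib dosing can be bounded but not read

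*Protocol*

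**What the plan says.** Under the heading on the primary safety endpoint, the supplement's detailed statistical methods list the summaries by arm and by three intervals: day 0-84, day 85-154 and day 155-238. Beyond the overall counts, they report the number and the "proportion of participants with AE, SAE, SUSAR, severe AEs, and AEs leading to study drug discontinuation by system organ class (SOC") and by PT. The analysis is descriptive: "No formal statistical testing of differences between the study arms was performed".

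The main listing in Supplementary Table 9 is headed "AE by System Organ Class (SOC) and Preferred term (PT) ([no. of events] no of patients (% of patients"). Supplementary Tables 10 and 11 have the same layout for the later intervals.

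On expected harm, section 7.2.7 says that the known reaction profile of etoricoxib would "give reason to expect gastrointestinal AEs, especially nausea, as the most common". Section 8.2 puts headache beside it: "Gastrointestinal EAE and headache are the most commonly occurring". Etoricoxib is given from day 0 to day 140, so the first two intervals contain all of the dosing.

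**The concern.** In the all-AE listings the SOC name stands on the line of its first PT, and each cell of events and participants refers to that one PT. No line gives the number of participants with at least one event in the SOC. The summary tables count participants over all SOCs together.

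This matters most for gastrointestinal disorders. In day 0-84 they are spread over ten PTs, and most cells are empty or hold one or two participants. Any-AE proportions are 85% to 92% in every arm and do not distinguish the arms. The proportion with at least one gastrointestinal event lies between these two levels, and it is a natural reading of what the methods announce. Headache does not have this problem, because it is a single PT and can be read directly.

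**Working it through.** **Is the listing complete?** The bracketed event counts of all PT rows in Supplementary Table 9 add to 58 (etoricoxib), 45 (vaccine), 54 (control) and 52 (combination). These are exactly the totals in the summary table. No PT row has been lost, and the listings in this document contain no SOC row.

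**Can the PT rows be added?** No. The etoricoxib gastrointestinal rows for day 0-84 hold eight PTs with one participant each and nausea with six: 8 × 1 + 6 = 14 participants. The arm has 13, of whom 11 had any AE. Some participants therefore appear on more than one row.

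**Bounds.** For each arm:
- lower bound = the largest participant count on any single gastrointestinal PT (all other events fall in the same participants);
- upper bound = the smaller of the sum of PT participant counts and the number with any AE.

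Day 0-84:

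| Arm | PT participant counts | Sum | Any AE | Participants with any GI event | GI events |
|---|---|---|---|---|---|
| Etoricoxib (13) | 1 × 8, 6 | 14 | 11 | 6-11 (46-85%) | 8 + 7 = 15 |
| Vaccine (12) | 1, 1, 2, 1, 4, 1 | 10 | 11 | 4-10 (33-83%) | 1 + 1 + 3 + 1 + 4 + 1 = 11 |
| Control (12) | 2, 2, 3 | 7 | 11 | 3-7 (25-58%) | 2 + 2 + 3 = 7 |
| Combination (10) | 1, 2, 5, 1 | 9 | 9 | 5-9 (50-90%) | 1 + 2 + 6 + 1 = 10 |

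Day 85-154: etoricoxib 1-2 of 11, vaccine 1-3 of 11, control 1-4 of 10, combination 1-3 of 8.

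Day 155-238: etoricoxib 2-4 of 10. The other arms have at most one gastrointestinal PT, so their counts are exact: vaccine 1 of 11, control 0 of 9, combination 1 of 8.

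**What can still be compared for day 0-84.** Event totals are exact: 15/13 = 1.15 per participant on etoricoxib, 11/12 = 0.92 on vaccine, 7/12 = 0.58 in controls and 10/10 = 1.00 on the combination. Nausea is given by participant: 6/13, 4/12, 3/12 and 5/10. Headache is too: 6/13, 5/12, 2/12 and 1/10.

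**Discontinuations, day 0-84.** The summary and the listing disagree:
- Events in the summary: 2, blank, 1, 7 (etoricoxib, vaccine, control, combination).
- Events in the listing: etoricoxib 1 + 1 + 1 + 1 + 3 = 7, vaccine 0, control 0, combination 1 + 1 + 1 = 3.
- Participants: the summary gives 4 for the combination, but the listing has only three rows of one participant each. The summary's one control participant is absent from the listing.

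**The case against.** Several counter-arguments are sound and limit the point.

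- The defined primary outcome is the occurrence of AEs, SAEs and SUSARs by interval. Those counts are in the summary tables and are unaffected. The SOC and PT description is supplementary and carries no tests.
- The wording can also mean PTs grouped within SOC, and the tables do deliver that. Even so, the proportion affected by the expected class of harm remains unavailable.
- In the SAE, SUSAR and severe-AE listings no SOC has more than one PT in any arm, so nothing is lost there.
- These are completed results in a supplement. Section 10.4.1 does not mention SOC, and table layout is usually left to an SAP, which is not shown. This bears on where to make the correction. It does not remove the gap between the supplement's methods text and its tables.

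A reader might go further and infer that the gastrointestinal comparison is wholly open. Pooling the two etoricoxib arms gives 11-20 of 23, against 7-17 of 24 without etoricoxib. The difference could then be anything from 47.8 - 70.8 = -23 to 87.0 - 29.2 = +58 percentage points. The documents do not support that inference. Those ends require complete overlap of terms in one pool and maximum spread in the other, so they are logical limits and not plausible values. Safety was planned by arm; this pooling is specified only for the day 0-84 immunogenicity comparison. Gastrointestinal events per participant are known, and each etoricoxib arm is above each arm without it.

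**Conclusion.** The point holds in a limited form. For day 0-84 and day 85-154 in all arms, and for day 155-238 in the etoricoxib arm, the proportion of participants with any gastrointestinal event can be bounded but not read. The day 0-84 bounds are wide: 6-11 of 13, 4-10 of 12, 3-7 of 12 and 5-9 of 10 (etoricoxib, vaccine, control, combination).

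The documents do not show that the primary safety outcome is unreported, that gastrointestinal harm cannot be compared at all, or that its direction is unknown on every measure. Event totals and nausea by participant are exact, and both are higher in each etoricoxib arm than in either other arm in day 0-84.

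The bounds assume that the PT participant counts are correct and that a participant is counted once per PT. The conclusion concerns the tables in this document; the SAP and the main article are not available. This is an inexpensive improvement in reporting and does not change any analysis.

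**What to change.** Add to Supplementary Tables 9 to 11 one descriptive row per SOC, giving events and participants counted once (n, %), by arm and interval. Do this for all AEs, severe AEs and AEs leading to discontinuation. For severe AEs the row will repeat figures that can already be read, but it keeps the layout uniform.

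Before adding the discontinuation rows, reconcile the day 0-84 event counts in the summary (2, blank, 1, 7) with those in the listing (7, 0, 0, 3), and the participant counts with them. Check Supplementary Table 10 too: its summary row is labelled as a number of AEs and shows 1 (9.1%) for the vaccine arm, while the listing has two events. These agree only if the summary entry counts participants.

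Do not add to section 10.4.1 a rule that makes SOC the level at which arms are compared. With results known, that would be a retrospective hierarchy. If the SOC rows are highlighted, label them descriptive and post hoc.

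Cost: one row per SOC from events already coded in MedDRA, plus the reconciliation. No new data are needed.
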